## 2.4 Recruitment strategy

Patients with LBP visiting Physiotherapy OPD of JSS Hospital, Mysuru, India and patients who are part of the community outreach programs of JSS College of Physiotherapy in Mysuru, will be invited to participate in this study. The convenience sampling will be followed for the recruitment. Individuals who express interest in the study will be given detailed information regarding their involvement and the specifics of the study.

## 2.5 Sample size estimation

Sample size was calculated using G power using input parameters such as an effect size of 0.5, and power of 0.95. A sample size of 154 was received as an output from G power, allowing for loss to followup.

## 2.6 Participants

The initial selection criteria outlined in Table 1. Eligible patients will be informed about the study and will be invited to participate by signing a written informed consent before being enrolled.

| **Inclusion criteria** |
| --- |
| 1. A primary complaint of either:   1. low back pain, defined as pain between the inferior costal margin and the inferior gluteal fold with or without referral into the leg(s),   or   1. referred leg pain, defined as predominately unilateral posterior leg pain extending below the knee, or anterior thigh pain, with or without back pain (disc herniation with associated radiculopathy subgroup only)   2. Duration of the current episode of primary complaint lasting for greater than 3 months (chronic stage of the injury)  3. Aged between 18 and 65 (inclusive)  4. Fluency in English sufficient to complete questionnaires and to enable understanding of the intervention  5. Agreeing to refrain from other interventions wherever possible for the 10-week treatment period of the trial, aside from consultations with medical practitioners, medication, and any exercises already being undertaken. |
| **Exclusion criteria** |
| 1. Active cancer under current treatment, as the treatment of cancer may interfere with their ability to participate in the trial  2. Signs of cauda equina syndrome based on bladder or bowel disturbance and/or imaging [52]  3. Current pregnancy, or childbirth within the last 6 months, as this could impair the ability to undertake exercises, and could also cause back and leg symptoms that are not related to the subgroups under investigation  4. Spinal injections within the last 6 weeks, as we wish to study treatment effects independent of the effects of injections  5. Any history of lumbar spine surgery, as there is already considerable research evaluating the efficacy of post-surgical rehabilitation programs  6. A pain intensity score of less than 2/10 on a 0-10 numerical rating scale due to low severity  7. Minimal activity limitation, evidenced by a baseline ability to walk, sit, and stand for one hour or more and no sleep disturbance at night, as we wish to exclude people with low severity  8. Already received more than 5 sessions of physiotherapy with any of the treating physiotherapists before enrolment, as these therapists are likely to use many components of the trial treatment protocol on their usual client caseload  9. Inability to walk safely, such as severe foot drop causing regular tripping, as the interventions in the trial include walking for most participants  10. Planned absence of more than one week during the treatment period (such as overseas holidays) |

**Table 1: Eligibility criteria common to all subgroups**

## 2.7 Therapist

Registered physiotherapists in India, who are currently involved in LBP management, and undergone a STOPS training course led by the original Australian developers ([name], and [name]).

## 2.8 Baseline evaluation

In addition to demographic and general health information of the participant, all the outcome measures (Table 2) provided below will be evaluated at baseline for both STOPS group as well as standard physiotherapy group. All the baseline assessment will be performed by a Physiotherapist who has a minimum of bachelor level degree and blinded allocation of the groups.

| **Patients’ outcome measures** | |
| --- | --- |
| **Outcome measures** | **Measurement points (**weeks) |
| **Primary outcome measures** | |
| 1. Oswestry Disability Index V2.1 with “sex life” question replaced by a “work/housework” question | 0, 5, 10, 26 and 52 |
| 2.Back pain and leg pain intensity :NPRS | 0, 5, 10, 26 and 52 |
|  |  |
| 3. Resting state functional MRI | 0,26 |
| **Secondary outcome measures** | |
| 1. Brief Pain Inventory | 0, 5, 10, 26 |
| 1. Global rating of change scale (7-point Likert scale) | 5, 10, 26 |
| 1. Satisfaction with treatment (5-point Likert scale) | 5, 10, 26 |
| 1. Interference with work or housework in the past week (5-point Likert scale) and number of hours missed at work in past week. | 0, 5, 10, 26 |
| 1. Örebro Musculoskeletal Pain Screening Questionnaire (ÖMPSQ-SF) | 0, 5, 10, 26 |
| 1. Quality of life (EuroQol-5D-5L) | 0, 5, 10, 26 |
| 1. Depression Anxiety and Stress Scale (DASS-21) | 0, 5, 10, 26 |
| 1. Pain Self-Efficacy questionnaire (PSEQ) | 0, 5, 10, 26 |
| 1. Pain Catastrophizing Scale (PCS) | 0, 5, 10, 26 |
| 1. Insomnia Severity Index (ISI) | 0, 5, 10, 26 |
| 1. Central Sensitisation Inventory (CSI) | 0, 5, 10, 26 |
| 1. Clinical inflammation score | 0, 5, 10, 26 |
| 1. Treatment Credibility Questionnaire | 5, 10, 26 |
| 1. Healthcare utilisation | 5, 10, 26 |
| 1. Compliance with treatment | 5, 10, 26, 52 |
| 1. Resting state functional MRI | 0, 26 |
| 1. Qualitative interviews | At the end of treatment trial 10 |
| 1. Adverse event | 5, 10, 26 |

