***Primary outcomes***

Activity limitation will be evaluated using nine questions from the Oswestry Disability Index Version 2.1^[66,67]^, with the tenth question relating to “sex life” being replaced by a question relating to “work/housework”.^[67,68]^ The Oswestry is a reliable, valid, and responsive instrument for measuring activity limitation in people with low back pain and referred leg pain.^[69-71]^

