***Secondary outcomes***

1. *Back pain and leg pain intensity:* Separate 0-10 Numerical Rating Pain Scales will be administered, one for back pain and another for leg pain. The intensity of pain will be rated on average over the past week, with end-point descriptors of “no pain” and “worst pain possible”.
2. *Pain severity and impact:* Brief Pain Inventory - Short Form (BPI-SF) will be used to assess the severity of pain and the impact of pain on daily functions. The BPI-SF is a 9-item self-administered questionnaire which exists within the [biopsychosocial model](https://www.physio-pedia.com/Biopsychosocial_Model) of pain, as it addresses sensory, emotional, and functional aspects of the pain experience ^[72]^. Thus, the tool is responsive to changes in pain associated with both pharmacological, physical, and psychological interventions^[73]^
3. *Global effect:* Global rating of change will be measured using a 7-point Likert scale, with participants rating their overall change since the baseline assessment as “completely recovered”, “much improved”, “slightly improved”, “no change”, “slightly worsened”, “much worsened”, or “vastly worsened”.^[74-75]^ Various versions of this scale are reliable, responsive, and valid. ^[75-76]^
4. *Satisfaction with treatment:* Participants will rate their satisfaction with physiotherapy treatment on a 5-point Likert scale, with ratings from “very satisfied” to “very dissatisfied”.^[77,78]^This scale has good reliability, validity, and responsiveness. ^[79,80]^
5. *Work interference:* Interference with work due to the LBP will be assessed in two ways. Firstly, at each assessment point, participants will record the number of workdays missed due to their back/leg condition over the previous 30 days. ^[14,56]^ Secondly, participants will rate the degree of interference with work (employment or housework) caused by their back/leg condition over the previous week on a five-point scale ranging from “not at all” to “extremely”. ^[14,56]^ These measurement methods have demonstrated good reliability, validity, and responsiveness ^[81,82]^.

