16. *Compliance with treatment:* The number of treatment sessions attended, and the number of missed or cancelled appointments by each patient will be recorded by the physiotherapists. Patient compliance with the treatment will be reviewed by the physiotherapists at each follow-up visit via direct questioning (on a scale of 0-10, how adherent have you been with following the advice and exercises recommended by your physiotherapist on average over the last month? from “not at all” to “fully”) and by reviewing the patient’s exercise charts ^[14,56]^.
17. Resting state functional MRI data (only for a cohort).Details under (Appendix 4)
18. *Qualitative interviews:* A qualitative study of therapist and patients’ experiences will be nested within the usual care program and quality improvement programme using a semi-structured questionnaire and interviews. Individual interviews lasting for 30-40 minutes will be conducted by a different researcher who has experience in qualitative interviews but was not involved in treating patients in the study. Interviews will be voice recorded, and transcribed verbatim, before undergoing thematic analysis. All discussions will be directed by a flexible topic guide (Appendix 3) developed from the pertinent literature ^[110-113]^. The topic guide comprises semi-structured non-leading questions phrased in clear language.
19. *Adverse events:* Continuous clinical assessment of adverse effects events (harmful or unpleasant) of treatment will be monitored by treating physiotherapists and recorded in their participant clinical notes, per their standard clinical practice. Physiotherapists will routinely enquire with participants each session about their response to treatment and any adverse effects of treatment or prescribed exercises.

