## 2.13 Follow-up

Patients will be assessed using self-administered questionnaires that will be filled in physically at the clinic at baseline, at the 5-week and 10-week treatment sessions, and then at the 26- weeks and 52-weeks (for only primary outcomes: disability) post-enrolment.

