***Analysis of patients’ clinical outcomes***

A descriptive summary of the characteristics of the patients will be provided at baseline. Continuous outcomes for patients will be analysed using linear mixed models (group × time interaction, with time modelled as a repeated measure) adjusting for baseline score. Ordinal outcomes will be analysed using the Mann-Whitney U test, while the risk ratio and number needed to treat will be evaluated using χ2 analyses. Analyses will focus on detecting between-group effects (with 95% CIs) at each time point (5, 10, and 26 weeks), and participants will be dichotomized according to whether they achieve the minimal clinically important difference (MCID) on outcome measures or not. The MCID for participants will be defined as 10/100 points for the Oswestry, 2/10 for the BPI pain scales, at least ‘much improved’ on the global rating of change scale, and ‘very satisfied’ on the treatment satisfaction scales. Given that these values may be too low in some contexts, the analyses will be repeated using a threshold of 50% reduction in Oswestry and NRS pain scores [14,56]. All data will be analysed according to intention-to-treat analysis (ITT), with missing data handled via maximum likelihood estimation ^[114]^.

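### Table 2 and section 2.12 give incompatible lists of primary outcomes, and no section says which outcome and visit decide the trial

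*Protocol*

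**What the plan says.** Table 2 in section 2.8 has three entries in its primary block: "1. Oswestry Disability Index V2.1 with “sex life” question replaced by a “work/housework” question", "2.Back pain and leg pain intensity :NPRS" and "3. Resting state functional MRI". The first two are scheduled at weeks 0, 5, 10, 26 and 52, and fMRI at weeks 0 and 26. The secondary block of the same table contains fMRI a second time.

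Section 2.12 differs. Its primary heading holds one instrument: "Activity limitation will be evaluated using nine questions from the Oswestry Disability Index Version 2.1". Pain intensity is item 1 of the secondary outcomes ("Separate 0-10 Numerical Rating Pain Scales will be administered, one for back pain and another for leg pain"), and imaging is item 17 ("Resting state functional MRI data (only for a cohort").

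Section 2.13 describes the last assessment as "52-weeks (for only primary outcomes: disability) post-enrolment". In section 2.15 the clinical analysis is described as follows: "Analyses will focus on detecting between-group effects (with 95% CIs) at each time point (5, 10, and 26 weeks". That section names neither a primary outcome nor a primary visit. Section 2.5 gives an effect size of 0.5 and power of 0.95 without saying which outcome or visit they refer to.

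**The concern.** The primary outcome fixes, before any data are seen, what result will count as showing that STOPS works. Here the protocol fixes it twice, in different ways. If the Oswestry difference is null and the leg pain difference is not, a reader of Table 2 may call the trial positive and a reader of section 2.12 must call it negative. The reverse can also happen: Table 2 does not say whether all of its primary outcomes must succeed or whether one is enough, so a positive Oswestry with null pain is a success under 2.12 and possibly a failure under Table 2.

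The protocol's own literature review shows that this divergence is realistic. As summarised there, the earlier Australian trial of individualised physiotherapy against advice favoured individualised care on the Oswestry at 10, 26 and 52 weeks, but on back and leg pain at 5, 10 and 26 weeks. At week 5 or week 52 the answer depended on which outcome was read. Section 2.2 says the present trial will be registered and reported to CONSORT, and both need one unambiguous primary outcome.

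**Working it through.** **Step 1. Set the sections side by side.**

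| Outcome | Table 2 | Section 2.12 | Section 2.13, week 52 | Section 2.15, visits in focus |
|---|---|---|---|---|
| Oswestry | Primary; weeks 5, 10, 26, 52 | Primary | Collected | 5, 10, 26 |
| Back and leg pain NPRS | Primary; weeks 5, 10, 26, 52 | Secondary, item 1 | Not collected | 5, 10, 26 |
| Resting-state fMRI | Primary and secondary; week 26 | Secondary, item 17, a cohort only | Not collected | Separate, within-group analysis |

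The pain and fMRI rows conflict on status. The pain row also conflicts on whether week 52 is collected, so the discrepancy reaches the visit schedule. Table 2 schedules compliance at week 52 as well, which 2.13 would exclude. The Oswestry is collected at week 52 under both sections, yet that visit is outside the stated analysis focus.

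**Step 2. Can the sample size settle which list governs?** With d = 0.5, power 0.95, an assumed alpha of 0.05 and a plain two-sample t-test, the total before dropout is 210 two-sided or 176 one-sided. Section 2.5 states 154 including dropout. The stated figure is not reproduced under these assumptions, and no outcome is attached to it, so it does not identify the primary outcome. Whether 154 is adequate is a separate question.

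**Step 3. What the two open choices could cost in false positives.** Assumptions, none of them given by the protocol:
- each between-group test is at two-sided 5%;
- any one significant result counts as success;
- the test statistics are jointly normal, with a common correlation between outcomes of 0.3 to 0.6 and between visits of 0.5 to 0.7, and for different outcomes at different visits the product of the two.

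The outcomes counted are the Oswestry, back pain and leg pain. The visits are 5, 10 and 26 weeks. The quantity is the probability under the null that at least one |z| exceeds 1.96. The correlated columns come from simulation with 400,000 draws (simulation error about 0.001). The independent column is 1 − 0.95^k for k tests.

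| Tests that could decide | Correlations (outcome, visit) 0.3, 0.5 | 0.5, 0.6 | 0.6, 0.7 | Independent |
|---|---|---|---|---|
| 1 outcome, 1 visit | 0.050 | 0.050 | 0.050 | 0.050 |
| 3 outcomes, 1 visit | 0.136 | 0.126 | 0.118 | 1 − 0.95^3 = 0.143 |
| 1 outcome, 3 visits | 0.124 | 0.117 | 0.109 | 1 − 0.95^3 = 0.143 |
| 3 outcomes, 3 visits | 0.317 | 0.278 | 0.245 | 1 − 0.95^9 = 0.370 |

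The conflict between the two lists accounts for the second row, about 12 to 14%. The lack of a named visit accounts for the third row, about 11 to 12%, and would remain if the Oswestry were the sole primary outcome. The last row combines the two.

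**The case against.** The strongest reply is that sections 2.12 and 2.13 both point to disability, so Table 2 is the outlier and the intention is clear enough. Part of this stands: the primary outcome is contradictory rather than wholly absent. It does not close the matter. Table 2 is the protocol's only complete schedule of outcomes and visits, and pain as co-primary is a plausible intention. The earlier Australian trial had the Oswestry and both pain scales as primary outcomes, and Table 3 gives the purpose of STOPS as improving pain as well as activity limitation.

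A second reply is that the SAP may name the decisive visit and any multiplicity rule. That is fair for those details taken alone. It does not cover two conflicting lists in the protocol, which would still contradict each other whatever the SAP chose.

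A reader might also infer more than the documents support:
- That the sample size implies a 5% error rate which is then broken. Section 2.5 states no alpha, sidedness, outcome or visit; the 5% used here is an assumption.
- That fMRI is a further route to a positive trial. It is planned in a cohort only, with one follow-up scan, and the only second-level analysis specified in section 2.15 is within group. As written it gives no comparison of the randomised arms.
- That section 2.13 declares disability the only primary outcome. It limits what is collected at week 52, which supports that reading without stating it.
- That the 24 to 32% is the effect of the conflicting lists. It also includes the separate gap of no named visit.
- That the protocol adopts a rule under which any significant result wins. It states no such rule; section 2.15 describes mixed models with between-group effects and 95% confidence intervals. The percentages show what is possible if the choice stays open.

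**Conclusion.** The contradiction is in the current text and no other section resolves it, so it must be corrected. The same results could be declared a success under Table 2 and a failure under section 2.12, or the reverse. With tests at an assumed two-sided 5% and any significant result counting, the conflict over outcomes alone gives about a 12 to 14% chance of a false-positive primary result at a single visit. With the visit also open across 5, 10 and 26 weeks, the chance is about 24 to 32%. These sizes rest on assumed correlations and on a decision rule that the protocol does not state. The contradiction itself depends on none of them.

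**What to change.** Make Table 2 agree with section 2.12: keep the Oswestry as sole primary outcome, move back and leg pain NPRS to the secondary block, and delete the fMRI row from the primary block so that it appears once, as secondary. If the sponsor intends pain as co-primary, change section 2.12 instead. It should then say whether one or all of the primary outcomes must succeed and, where one suffices, state the multiplicity adjustment. fMRI should leave the primary block in either case, because it covers only a cohort and its planned analysis is within group.

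In section 2.15, name one decisive visit; which one is the sponsor's choice. Make sections 2.13 and 2.15 and Table 2 agree on whether week 52 is collected and analysed, and for which outcomes. Report the remaining outcomes and visits as supportive estimates with confidence intervals.

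The cost is wording, and no new data are needed. Under the first option, pain can no longer be claimed as an unadjusted primary result. Under the co-primary option where any one outcome suffices, a Bonferroni split over the three outcomes lowers the power for each at N = 154 from 0.87 to 0.75 (d = 0.5, two-sided t-test, no dropout, no baseline adjustment).

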### 2.10.2 Usual care group

Participants in the usual care receive the routine physical therapy regimen of 10 sessions over 10 weeks

| **Intervention description:** | | | |
| --- | --- | --- | --- |
|  | STOPS physiotherapy | Usual physiotherapy care |  |
| Brief name | STOPS | Usual care |  |
| Why | Improve pain and activity limitation by addressing each participant’s individual barriers to recovery, with better maintenance of treatment effects in the long-term | Short-term relief of pain and function through traditional treatment methods that meet the expectations of participants |  |
| What materials | STOPS treatment protocols.  Decision-making flowcharts.  Treatment based on thorough assessment and questionnaire battery. | Usual care treatment as per protocols followed in Physiotherapy Outpatient Department (OPD) of JSS Hospital, Mysuru, India. |  |
| What procedures | In accordance with published STOPS protocols, modified for persistent pain. | Usual treatment procedures at discretion of physiotherapist |  |
| Who provided | Physiotherapist who has received training in the STOPS approach for managing persistent low back pain | Physiotherapists unfamiliar with the STOPS approach |  |
| How provided | Individual face-to-face sessions | Individual face-to-face sessions |  |
| Where (setting) | Participant with chronic LBP living independently in the community. Treatment provided at Federal Physiotherapy Outpatient Department (OPD) of JSS Hospital, Mysuru, India and the associated community centers affiliated to JSS Hospital. | Participant with chronic LBP living independently in the community. Physiotherapy Outpatient Department (OPD) of JSS Hospital, Mysuru, India and the associated community centers affiliated to JSS Hospital. |  |
| When/how much (dose) | 11 x 45-minute sessions (10sessions in 10 weeks) and the 11^th^ at 6-months post trail commencement | 11 x 45-minute sessions (10 sessions in the 10 weeks) and the 11^th^ at 6-months post trail commencement |  |
| Tailoring | Sessions tailored to the needs and progress of the individual in accordance with the STOPS protocols and detailed assessment profile of the participant | Sessions tailored to the needs and progress of the individual based on standard procedures used by the physiotherapist |  |

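### Adverse-event collection stops at week 26, when the last treatment session takes place, so events after that session are not recorded as adverse events although Table 2 follows disability and pain to week 52

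*Protocol*

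**What the plan says.** - **Schedule.** Table 2 (section 2.8) lists "Adverse event | 5, 10, 26". There is no week-52 entry.
- **Method.** Section 2.12, secondary outcomes, item 19, calls the assessment continuous and says that events "will be monitored by treating physiotherapists and recorded in their participant clinical notes, per their standard clinical practice". On timing: "Physiotherapists will routinely enquire with participants each session about their response to treatment and any adverse effects of treatment or prescribed exercises". It describes no other source of adverse-event data.
- **Last session.** Table 3 gives both arms 11 sessions: 10 in the first 10 weeks and the last "at 6-months post trail commencement".
- **Week-52 contact.** Section 2.13 describes self-administered questionnaires completed at the clinic, and has the last of them at "52-weeks (for only primary outcomes: disability) post-enrolment".
- **Other week-52 entries.** Table 2 runs Oswestry to week 52, and also pain ("Back pain and leg pain intensity :NPRS | 0, 5, 10, 26 and 52") and compliance ("Compliance with treatment | 5, 10, 26, 52"). Healthcare utilisation ends at week 26.
- **Session count in the text.** Section 2.10.2 says "Participants in the usual care receive the routine physical therapy regimen of 10 sessions over 10 weeks". Section 2.10.1 likewise places the STOPS sessions within 10 weeks. Neither narrative mentions the 11th session.

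**The concern.** The final adverse-event point and the final treatment session fall at about the same time. Because enquiry about harm is tied to sessions, nothing is set up to record an event that follows the 11th session, in either arm. The trial nevertheless sees participants again at week 52 to measure efficacy outcomes.

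Table 3 gives better long-term maintenance of effect as part of the rationale for STOPS. Any long-term statement on disability or pain would have no matching record of harm. A hospital admission or operation between weeks 26 and 52 would not be picked up through healthcare utilisation either, since that also stops at week 26. An analysis plan cannot repair this, because the data would not have been collected.

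**Working it through.** The protocol gives no figure to reproduce. The check compares the schedule passages and needs only timeline arithmetic.

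**Inputs**
1. Adverse-event points: weeks 5, 10 and 26 (Table 2).
2. Ascertainment: enquiry by the treating physiotherapist at each session (2.12, item 19).
3. Last session: 6 months, both arms (Table 3).
4. Week-52 contact: disability only (2.13).
5. Last efficacy point: week 52 for Oswestry and back and leg pain (Table 2).

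**Steps**
1. Last session in weeks: 6/12 × 52 = 26, so about week 26.
2. Scheduled adverse-event window after the last session: 26 − 26 = 0 weeks, approximately.
3. Follow-up without adverse-event collection: 52 − 26 = 26 weeks, and 26/52 = 50%.
4. Does the continuous monitoring in item 19 extend the window? It works through enquiry at sessions, and no session is scheduled after month 6. It does not.
5. Does the week-52 contact extend it? Table 2 has no adverse-event entry there, and 2.13 restricts that contact to disability. The two passages agree in leaving harms out.
6. What could still show a problem at week 52? Oswestry and, according to Table 2, the pain scales. They would register lasting worsening, but not what happened or whether treatment was thought to be the cause.

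**Conflicts found on the way**
- *Week 52.* Table 2 includes pain and compliance; 2.13 allows only disability. If 2.13 is followed, only Oswestry remains as an indirect signal.
- *Session count.* The narratives of both arms cover 10 weeks, while Table 3 has an 11th session at 6 months. If the narratives were followed, item 19's enquiry would end at week 10 in both arms, and the week-26 adverse-event entry would have no session behind it.
- *Order at week 26.* The protocol does not say whether week-26 collection comes before or after the 11th session, so an event arising during or just after that session could be missed.

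**The case against.** The case for leaving the plan alone is that Table 2 and 2.13 do not contradict each other on adverse events. Almost every other secondary outcome with numbered weeks also ends at 26. Collection covers the whole 10-session block and continues to week 26, with enquiry about both treatment and prescribed exercises. Only one further session and any later home exercise lie beyond it, and the documents give no rate of delayed harm from either. Section 2.15 names only weeks 5, 10 and 26 for between-group effects, so the stated analysis horizon matches the adverse-event horizon. Adding harms at week 52 would also mean a different method, patient report instead of therapist enquiry, with long recall.

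Much of this stands. It limits the point to events after the 11th session and makes this a design choice that can be improved cheaply. It does not close the gap: Table 2 collects efficacy data at week 52, and no passage collects harms after week 26.

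Three stronger readings are tempting and should not be drawn:
- *That the harm window differs between arms,* ending at week 10 in usual care and week 26 in STOPS. This takes the narrative for one arm and Table 3 for the other. Read consistently, either source treats the arms alike, and Table 2's adverse-event points apply to both.
- *That the protocol itself treats exposure as continuing to week 52.* This rests on the week-52 compliance entry in Table 2, which 2.13 excludes. Continued home exercise after week 26 is at most implied.
- *That harm from home exercise is never captured.* Before the 11th session it is asked about at every session.

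**Conclusion.** The concern holds in limited form. Events after the 11th session, in the 26 weeks (50% of follow-up) between weeks 26 and 52, are not recorded as adverse events in either arm. Worsening would appear only in the week-52 Oswestry and, if Table 2 is followed, pain scores.

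This rests on reading 6 months as about week 26, on Table 3 for the timing of the last session, and on item 19 being the only method of ascertainment, as the protocol describes no other. How many events would be missed cannot be estimated, because the documents give no event rate. The gap does not affect the efficacy comparison. It limits what can be said about long-term harm and should be corrected because the correction is cheap.

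**What to change.** 1. Add 52 to the adverse-event row of Table 2, and amend 2.13 so that the week-52 questionnaire in both arms carries one patient-reported adverse-event item. It should cover the time since the previous assessment and name serious events, admissions and surgery.
2. Report those events separately from therapist-recorded events, since the method differs.
3. State whether week-26 adverse-event collection comes before the 11th session, so that it is clear which assessment covers events arising from that session.
4. Reconcile Table 2 with 2.13 on what is collected at week 52, including pain and compliance.
5. Reconcile the 10-week narratives in 2.10.1 and 2.10.2 with the 11 sessions in Table 3.

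The cost is one questionnaire item at a contact already planned, plus wording changes. Recall over 26 weeks will miss minor events, and the week-52 data will not be directly comparable with those from weeks 5, 10 and 26.
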